### Study Setting

The study will occur in Zambia. Zambia is an eastern, sub-Saharan African country with an estimated 2021 population of 18,920,657 and nearly half of the population under the age of 15 years, with almost equal proportions of males and females (49.5% and 50.5%, respectively) [65]. Zambia covers about 290,587 square miles (743,390 km^2^), and the population’s median age is only 16.8 years [65,66]. The country is prone to natural and man-made disasters such as floods, droughts, mine accidents, and deforestation [49]. War and other political uncertainty in surrounding states result in a refugee influx. The study will focus on 4 main cities in Zambia: Livingstone, Lusaka, Kasama, and Solwezi. Livingstone is a capital city in the southern part of the country, with a land area of 85,283 km^2^ and a population of 1,799,885 in 2014. There were about 1241 basic schools in 2012 and 45 high schools in 2004. In 2014, there were 6158 teachers in school grades 1-9, and 1027 in high school [67].

Lusaka is the capital of Zambia and one of the 20 cities in Zambia, with a total land area of 375 km^2^ with an approximate population of 3,042,000 in 2022, a 4.68% increase from 2021 [68]. There were 111 secondary schools and 758 primary schools in Lusaka in 2017 [66], and about 10,822 primary school teachers and 3383 secondary school teachers in Lusaka in 2016 [66]. There are several rural cities in Zambia, including Kasama (Northern Province) and Solwezi (North Western Province). Kasama had a land area of 77,650 km^2^ and a population of 1,264,212 in 2014. There were 1208 basic schools and 26 high schools in 2004. In 2004, there were 5169 teachers in all schools, grades 1-9, and 656 teachers in high schools, grades 10-12 [67]. Solwezi has a land area of 125,826,656 km^2^, and a total population of 811,706 was recorded in 2014. Basic schools in 2012 were 747 and 23 high schools in 2004. Teachers in all schools in grades 1-9 were 2837 in 2004, while teachers in high schools in grades 10-12 were 509 the same year [67].

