### Sample Size Estimation

With the total teacher population in Lusaka, Livingstone, Kasama, and Solwezi of about 30,561 [66], using a web-based script [77], it is projected that the sample size needed for our prevalence estimates with 95% confidence and a 3% margin of error for moderate to high stress, burnout, moderate to high anxiety, moderate to high depression, and low resilience among teachers in Livingstone, Lusaka, Kasama, and Solwezi will be 993. Based on the maximum survey completion rate attained for the Text4Hope and Text4Mood programs in Alberta of 20% [50,78,79], to achieve an estimated 993 completed surveys at baseline, it is planned to enroll at least 4965 teachers in the Wellness4Teachers email supportive and mental health literacy messaging program within 12 months.

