### Statistical Analysis

SPSS (version 25; IBM Corp) [80] will be used to analyze the quantitative data from the surveys. Surveys with more than 50% missing responses will not be included in the data analysis. There will be no missing data imputation, and the analysis of the included survey responses and results will be based on completed survey data. Descriptive statistics for demographic, mental health literacy, clinical, and burnout-related variables will be provided. A 2-tailed *P*≤.05 will be used to determine statistical significance for all analyses, and descriptive characteristics will be presented as percentages and numbers. A chi-square test and logistic regression analysis will be used to separately identify demographic, clinical, and work-related correlates of anxiety, depression, stress, low resilience, and burnout for elementary and high school teachers. Significant and borderline significant variables from the chi-square analysis would be used to develop multivariable binary logistic regression models to predict the adjusted odds of outcomes for the exposure of interest and each potential correlate. The impact of the email supportive messaging program in reducing moderate to high anxiety, moderate to high depression, moderate to high stress, burnout, and improving resilience among subscribers will be evaluated by comparing the mean changes in these parameters from baseline to 6 weeks, 3 months to 6 months, and 12 months using the paired *t* test. To assess the effects of the intervention against a control group, we will choose a defined period of 3 months during the study period (for instance, the beginning of January 2023 to the end of March 2023) and compare the prevalence and mean scores on standardized scales for stress, anxiety, burnout, and depression at 6 weeks for subscribers who have received the daily supportive SMS text messages for 6 weeks (the intervention group) to the baseline prevalence and mean scores on the same scales for new subscribers during the period (the control group).

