### Hypothesis

Based on the greater than 20% reduction in depression symptom scores in the intervention group compared to the control group in 2 randomized controlled trials in Ireland and Canada [56,57], and the greater than 20% reduction in anxiety symptom scores from baseline to 6 weeks and 3 months in subscribers of Text4Hope [51,52], we hypothesize that the Wellness4Teachers email messaging program will reduce the prevalence and severity of stress, burnout, anxiety, depression, and low resilience symptoms among Zambian teachers by at least 20%*.* We also hypothesize that the Wellness4Teachers email program will improve mental health literacy scores in the teachers subscribing to the program by at least 20%. In addition, we hypothesize that the prevalence of moderate to high stress, moderate to high anxiety, moderate to high depression, burnout, and low resilience would be comparable to the prevalence of these conditions reported in other jurisdictions [81,82]. Finally, we hypothesize that demographic factors, socioeconomic factors, organizational factors, and class size will be associated with burnout and other psychological disorders in teachers [16,19-23,49,58].

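### The only comparison with a control group is confined to one 3-month period of a 12-month enrolment, which leaves usable surveys out and, under even accrual, makes its intervals about 1.9 times as wide as they need be

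*Protocol article*

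**What the plan says.** The Statistical Analysis section gives two effectiveness analyses. One is a paired *t* test of change within subscribers, with no comparator. The other brings in a comparator: "we will choose a defined period of 3 months during the study period (for instance, the beginning of January 2023 to the end of March" (in 2023). Within that period, 6-week prevalence and mean scores of subscribers who have had six weeks of messages are set against baseline values of teachers newly subscribing.

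Recruitment is much longer than that: "it is planned to enroll at least 4965 teachers in the Wellness4Teachers email supportive and mental health literacy messaging program within 12 months". The Results section puts the launch in January 2023, so the example window opens at launch.

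The Hypothesis section expects that the programme "will reduce the prevalence and severity of stress, burnout, anxiety, depression, and low resilience symptoms among Zambian teachers by at least 20"%. The sample size serves a different aim, being the "sample size needed for our prevalence estimates with 95% confidence and a 3% margin of error". No sizing is given for the controlled comparison. The test level is stated once: "A 2-tailed *P*≤.05 will be used to determine statistical significance for all analyses".

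**The concern.** From about week 6 after launch until enrolment closes, the design produces both sides of this contrast continuously: new subscribers complete baseline surveys while earlier ones reach six weeks. Restricting the contrast to three months discards surveys that are eligible, contemporaneous and already paid for.

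This is the only analysis that sets the programme against any comparator. If its interval is too wide to tell no effect from the hypothesised 20% fall, the effectiveness evidence rests on an uncontrolled before-after test. The point concerns precision only. It would remain if the window were fixed in advance and the two groups contained different teachers.

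**Working it through.** **Inputs from the article.** Two-sided 0.05 (Statistical Analysis). A 20% reduction, read as relative, so p2 = 0.8 × p1 (Hypothesis). 993 completed baseline surveys (Sample Size Estimation). 12 months of enrolment (Results). Teacher prevalences of 25.3% (stress), 33.3% (burnout), 35.3% (depression) and 38% (anxiety), and 74% as the top of the burnout range (Background). 67.5% (anxiety, Egypt) and 81% (stress rated as often, Lusaka), also in Background.

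**Assumptions not in the article.** Even accrual; as many 6-week as baseline surveys (a best case); surveys treated as independent.

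**Step 1: the plan's own figure.** n0 = 1.96² × 0.25 / 0.03² = 1067. With the finite-population correction n0 / (1 + (n0 − 1)/N):
- N = 30,561, the stated four-city total, gives 1031, not 993.
- N = 10,822 + 3383 = 14,205, the Lusaka total in Study Setting, gives 993.

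993 / 0.20 = 4965 does reproduce. The discrepancy is a separate matter and hardly affects this point: a quarter of 1031 is 258 rather than 248.

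**Step 2: surveys per group.**
- Any 3-month window: 993 × 3/12 = 248.
- Example launch window: only teachers joining in about the first 7 of 13 weeks reach six weeks inside it, so 248 × 7/13 = 134 six-week surveys against 248 baselines.
- Whole overlap, week 6 to week 52: 993 × 46/52 = 878 of each.

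**Step 3: precision, with no prevalence or SD needed.** Interval width scales with 1/√n, so the ratio is √(878/248) = 1.88. It applies to prevalences and mean scores equally.

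**Step 4: power for a 20% relative fall in prevalence.** Power = Φ[(d − 1.96·SE0)/SE1], where d = p1 − p2, SE0 uses the pooled proportion and SE1 the separate ones. The 95% half-width is 1.96·SE1.

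Example at 35.3%: p2 = 28.24%, d = 0.0706.
- 248 per group: SE0 = 0.0418, SE1 = 0.0417, (0.0706 − 0.0819)/0.0417 = −0.27, power 39%.
- 878 per group: SE0 = 0.0222, SE1 = 0.0222, (0.0706 − 0.0436)/0.0222 = 1.22, power 89%.

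Each cell gives power, then half-width in percentage points:

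| Baseline | d (points) | 248 vs 248 | 248 vs 134 | 878 vs 878 |
|---|---|---|---|---|
| 25.3% | 5.1 | 27%, 7.4 | 19%, 8.7 | 72%, 3.9 |
| 33.3% | 6.7 | 37%, 8.0 | 26%, 9.5 | 86%, 4.3 |
| 35.3% | 7.1 | 39%, 8.2 | 28%, 9.7 | 89%, 4.3 |
| 38% | 7.6 | 43%, 8.3 | 31%, 9.9 | 92%, 4.4 |
| 67.5% | 13.5 | 87%, 8.5 | 74%, 10.3 | >99%, 4.5 |
| 74% | 14.8 | 94%, 8.2 | 84%, 10.0 | >99%, 4.4 |
| 81% | 16.2 | 98%, 7.7 | 93%, 9.4 | >99%, 4.1 |

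At 25-38%, the half-width with 248 per group exceeds the hypothesised difference. With 878 it does not. At 67.5% and above, the window's half-width is already smaller than the difference.

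**Step 5: varying the assumptions (baselines 25.3-38%).**
- 6-week response half of baseline: 18-30% (248 vs 124) against 53-78% (878 vs 439).
- 6-week response one fifth of baseline: 10-16% (248 vs 50) against 29-48% (878 vs 176).
- Half of all accrual inside the window (497 vs 497): 48-72%.
- Very low prevalence, 8.3% (the bottom of the stress range): 10% against 26%.

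**Mean scores.** Power cannot be set, because no SDs are given. As illustration only, 248 vs 248 gives 61% at a standardised difference of 0.2 and 92% at 0.3.

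**The case against.** The strongest reply is that the low power figures depend on which prevalences are used. Those at 25-38% are single-study values not identified as African, and the 25.3% refers to mild to moderate stress, whereas the outcome is moderate to high stress. The Egyptian and Lusaka figures are far higher and make the window adequate. This stands. A reader might infer that the comparison simply has 20-43% power, or would usually miss a true effect. The article does not support that without the condition on prevalence, and the inference leaves out mean scores, which the same sentence compares.

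Three further points stand in part.
- **Accrual.** No pattern is stated, so the loss of about three quarters of the surveys is an assumption, and January to March is only an example. Strong front-loading reduces the loss but does not remove it.
- **Size of the gain.** The 20% completion rate is described as a maximum, and Limitations expects less, so 878 six-week surveys is optimistic. The gain shrinks with lower response but remains. No power has been computed for the month-adjusted, clustered model.
- **Overlap of teachers.** Under even accrual, about 40/46 (87%) of 6-week respondents in the longer period also joined during it and could appear as controls, against about 7/13 (54%) in a mid-enrolment 3-month window. This must be modelled. Positive within-teacher correlation would tend to tighten the difference, so treating surveys as independent should not flatter the longer period.

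Finally, the primary outcomes are changes from baseline among subscribers, assessed by paired analyses that this window does not limit. That lowers the weight of the point. None of these replies shows that the restriction improves the comparison.

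**Conclusion.** The point holds in a conditional form. The article confines its only controlled comparison to three of twelve enrolment months, gives no precision reason, and so leaves out surveys it will already hold.

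Under even accrual and equal completion at both times, the cost is an interval about 1.9 times as wide for every outcome. For prevalence, it is the difference between 27-43% and 72-92% power if baselines are 25-38% (19-31% in the example launch window). If baselines are 67.5-81%, the 3-month window already gives 87-98%, and the gain is in precision rather than in detecting the hypothesised fall. The article fixes neither the baseline prevalence nor the 6-week response, so no single power figure can be attached to the plan.

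This is a worthwhile, inexpensive improvement of modest severity. It does not show that the study as a whole is underpowered.

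**What to change.** In Statistical Analysis, replace the single 3-month period with the whole overlap period, from 6 weeks after launch to the close of enrolment. Compare all 6-week surveys with all new-subscriber baseline surveys returned in that period. Fit one regression per outcome, logistic for prevalence and linear for scores, with calendar month as a factor so that the contrast stays contemporaneous, and with standard errors clustered by teacher. Retain the 3-month window as a sensitivity analysis.

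The cost is a short rewording and a slightly more complex model, with no extra participants or surveys. The longer period brings more calendar variation and more teachers in both groups. The month factor and the clustering deal with these.

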### Data Collection

Quantitative data will be collected using web-based questionnaires through the ResilienceNHope secure platform for managing web-based surveys and databases [57]. The web-based questionnaires will be designed to collect demographic and work-related variables and assess mental health literacy and clinical variables, including stress, burnout, anxiety, depression, and resilience [59]. The web-based surveys will be distributed to subscribers on enrollment at 6 weeks, 3 months, 6 months, and 12 months. The follow-up surveys will also include questions assessing subscriber experience and satisfaction with the Wellness4Teachers email messaging program.

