## Results

The Wellness4Teachers email messaging program is anticipated to be launched in January 2023. Enrollment will continue for 12 months, and data collection will continue for another 12 months. Results of the study will be disseminated to stakeholders in the education sector in Zambia, East African countries, and globally through workshops, conference presentations, and peer-reviewed publications.

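### The 6-week control-group comparison lets the same teachers be in both groups, because its 3-month window is longer than the 6-week exposure and nobody is excluded

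*Protocol article*

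**What the plan says.** The last sentence of Statistical Analysis (Protocol article, Methods) sets up a comparison with controls. The investigators will "choose a defined period of 3 months during the study period (for instance, the beginning of January 2023 to the end of March 2023"). Inside that period the intervention group supplies scores "at 6 weeks for subscribers who have received the daily supportive SMS text messages for 6 weeks (the intervention group"). These are compared "to the baseline prevalence and mean scores on the same scales for new subscribers during the period (the control group"). The scales are those for stress, anxiety, burnout and depression. No test is named for this comparison.

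Three other statements bear on it:

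- Data Collection makes clear that one set of subscribers is surveyed repeatedly: "The web-based surveys will be distributed to subscribers on enrollment at 6 weeks, 3 months, 6 months, and 12 months".
- Results gives the start: "The Wellness4Teachers email messaging program is anticipated to be launched in January 2023".
- Results also gives the enrolment period: "Enrollment will continue for 12 months, and data collection will continue for another 12 months".

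Nothing in the article keeps an intervention subscriber out of the control group, or requires intervention subscribers to have enrolled before the window opens.

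**The concern.** The idea of comparing people six weeks into the programme with people just entering it, over the same calendar period, is a sensible use of staggered enrolment. It works only if the two groups are different people, or if the analysis allows for those who are in both. Here a teacher who enrols early in the window gives a baseline that counts as control data and, six weeks later and still inside the window, a score that counts as intervention data.

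This matters because it is the only analysis with a control group; the other effect analysis is a paired t test on subscribers. To the extent that the groups share members, the controlled comparison is the same before-after change under another label. It then adds little protection against calendar effects such as the school term. A test that treats the groups as independent would also use the wrong variance.

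**Working it through.** The plan states no sample size, power or overlap figure for this comparison, so there is none to reproduce. The check is date arithmetic on the two group definitions.

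**Inputs.** From the document: example window 1 January to 31 March 2023 (31 + 28 + 31 = 90 days); exposure 6 weeks = 42 days; launch anticipated in January 2023; enrolment over 12 months. Assumed: uniform enrolment; within-person correlation ρ between baseline and 6 weeks of 0.5 to 0.7; equal variances at the two times.

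**Definitions.** Control: subscription date inside the window. Intervention: subscription date + 42 days inside the window. No subscription can precede launch.

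**Example window, launch on 1 January.**
- Last subscription date that reaches six weeks by 31 March: 31 March − 42 days = 17 February.
- Intervention enrolment days: 1 January to 17 February = 31 + 17 = 48.
- All 48 lie inside the 90-day control window, so 48/48 = 100% of intervention subscribers are also controls by subscription date.
- In the other direction, 48/90 = 53% of control enrolment days belong to intervention subscribers. The other 42 days (18 February to 31 March) are different people.

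**Later launch in January, same window.** The first share stays at 100%; the second falls.
- 15 January: 34 of 34 intervention days overlap; 34/76 = 45% of control days.
- 31 January: 18 of 18 intervention days overlap; 18/60 = 30% of control days.

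**Other readings of the example.** If the window limits subscription only, and 6-week surveys may come later, the two groups are one cohort. If intervention subscribers had to enrol before the window, the group would be empty. No reading gives two separate groups.

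**Later windows.** For a 90-day window well after launch, (90 − 42)/90 = 48/90 = 53% of each group is shared. Calendar quarters give about the same: April to June 49/91 = 54%; July to September 50/92 = 54%.

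**What the contrast then estimates.** Take the example window with launch on 1 January. Let I6 and I0 be the intervention subscribers' 6-week and baseline means, and L0 the baseline mean of those enrolling from 18 February. Then

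I6 − (48/90·I0 + 42/90·L0) = 0.53·(I6 − I0) + 0.47·(I6 − L0).

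Just over half the weight is the before-after change. On timing, 6-week scores fall between 12 February (1 January + 42 days) and 31 March, while control baselines start on 1 January.

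**Standard error.** With m shared people, the variance of the difference is proportional to 1/nI + 1/nC − 2ρm/(nI·nC); an independent-samples test omits the last term. Using enrolment days as relative sizes, nI = m = 48 and nC = 90:
- Independent-samples variance: 1/48 + 1/90 = 0.03194.
- ρ = 0.5: true variance 0.03194 − 0.01111 = 0.02083; ratio 0.652; SE too large by 1/√0.652 = 1.24.
- ρ = 0.6: 0.03194 − 0.01333 = 0.01861; ratio 0.583; SE too large by 1.31.
- ρ = 0.7: 0.03194 − 0.01556 = 0.01639; ratio 0.513; SE too large by 1.40.

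**The case against.** The strongest reply has five parts.

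- **The window is only an example and the launch only anticipated.** True, and the 100% figure depends on both. But a later 3-month window still shares about half of each group, because the cause is the window length relative to six weeks.

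- **The control group is not wholly the intervention group again.** This stands. A reader might infer that there is no independent control and that the analysis collapses entirely into the paired one. The dates do not support that: nesting runs one way, and controls from 42 of the 90 enrolment days are different people whose baselines are contemporaneous with the 6-week surveys. Calendar control is weak, not absent.

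- **Overlap by subscription date is not overlap in the data.** This also stands. Sample Size Estimation expects about 20% survey completion, and nothing requires a baseline before a 6-week response. Some 6-week respondents will have no baseline among the controls. The overlap percentages are therefore upper bounds. That is accidental separation, though, not a design.

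- **The variance error is conservative and hypothetical.** Correct: an SE that is too large makes a test too cautious, and no test is named. A reader might apply 1/√(1 − ρ) and get 1.41 to 1.83, but that needs two identical groups of equal size, which holds only if the window limits subscription alone.

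- **The comparison is supplementary.** Outcomes and Measures defines the primary outcomes as changes from baseline among subscribers, and this analysis covers one of four follow-up times. That bears on priority. It remains the only comparison offered as controlled.

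A reader might also infer that the window could be picked after seeing the data. The text says a defined period will be chosen, and its dates may be fixed in the full protocol or analysis plan, so the article does not support that charge.

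**Conclusion.** The concern holds. As defined, the intervention and control groups overlap: by subscription date, up to 100% of the intervention group in the example window, and up to about 53% in any later 90-day window under uniform enrolment. The comparison therefore largely repeats the uncontrolled before-after contrast (just over half its weight if launch is on 1 January, less if launch is later in the month) and gives weak control of calendar effects. If an independent-samples test were used, its standard error in the example window would be about 1.24 to 1.40 times too large, for an assumed correlation of 0.5 to 0.7. The loss of a clean control is the main harm; the variance error is secondary.

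One further inference should be resisted: that separating the groups would deal with regression to the mean. It would not. Controls are measured at the moment they choose to enter and the intervention group six weeks after theirs, so a fall from a high entry score would appear in a fully disjoint comparison too.

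**What to change.** Delete the January to March 2023 example and adopt one of two designs in advance.

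1. **Disjoint window.** Fix a window that starts at least 6 weeks after launch and lasts no more than 6 weeks. Intervention subscribers must have enrolled before it and controls within it. A teacher enrolling on the first day of a 42-day window reaches six weeks on the day after it closes, so no one can be in both groups. The cost is fewer surveys. Assuming uniform accrual of the planned 4965 over 365 days and 20% completion at each survey, 42 enrolment days give 4965/365 × 42 × 0.20 ≈ 114 completers per group. The overlapping example window would give about 245 control baselines (90 days) and 131 six-week surveys (48 days).

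2. **Full staggered enrolment.** Use all 12 months of enrolment and compare 6-week surveys with new subscribers' baselines in the same calendar month, in a mixed model or GEE with person as cluster and calendar month as covariate. This keeps the data and allows for teachers who contribute twice. The cost is slightly more modelling.

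Neither needs new data collection. Under either option, state in the protocol that regression to the mean from self-selected entry remains.

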## Methods

### Study Design

This will be an interventional study, specifically a quasi-experimental design, which will employ a quantitative longitudinal and cross-sectional survey methodology with data collected from subscribers of Wellness4Teachers email messaging service users.

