### Participants’ Recruitment and Subscription

Subscription to the Wellness4Teachers email messaging program will be initiated by individual teachers accepting an invitation to subscribe from the Lusaka Apex Medical University’s organizational account on the ResilienceNHope web-based application. The local principal investigator (CC) will work with the Zambian Ministry of Education, the Lusaka Teachers Association, district school boards, and heads of elementary and high schools to invite teachers to join the Wellness4Teachers email messaging program. Participants will be eligible for inclusion if they are school teachers and residents of Livingstone, Lusaka, Kasama, or Solwezi. Subscribers can unsubscribe from the program at any time by clicking the unsubscribe link associated with the messages. Based on the 10% dropout rate recorded for the Text4Hope program [51,52], the anticipated dropout rate for the email messaging program will be less than 15% [54].

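### The 6-week intervention-versus-control contrast compares staggered, partly overlapping sign-up cohorts with no adjustment stated, so a shift in teacher mix between them would read as a programme effect

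*Protocol article*

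**What the plan says.** Study Design states the design plainly: "This will be an interventional study, specifically a quasi-experimental design".

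Statistical Analysis then describes two ways of judging the programme. The first is paired t tests of within-subscriber change. The second is the contrast at issue here: "we will choose a defined period of 3 months during the study period", with January to March 2023 as the example. One side is "subscribers who have received the daily supportive SMS text messages for 6 weeks (the intervention group". The other is "baseline prevalence and mean scores on the same scales for new subscribers during the period (the control group". (The word SMS in an email programme is a separate wording matter.) The stated analysis is to "compare the prevalence and mean scores on standardized scales for stress, anxiety, burnout, and depression at 6 weeks for subscribers" in the first group and set the results against the second. No covariate, matching, weighting or stratification is mentioned.

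Adjustment does appear in the same section, but for the correlates of each condition: "multivariable binary logistic regression models to predict the adjusted odds of outcomes for the exposure of interest and each potential correlate".

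Three other places bear on the point:

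- Under Participants' Recruitment and Subscription, the local principal investigator "will work with the Zambian Ministry of Education, the Lusaka Teachers Association, district school boards, and heads of elementary and high schools" to reach teachers in four cities. The Results section gives 12 months for enrolment.
- Under Data Collection, the questionnaires are "designed to collect demographic and work-related variables and assess mental health literacy and clinical variables".
- Under Hypothesis, the protocol expects teacher, socioeconomic and organisational characteristics and class size to be related to burnout and the other outcomes.

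**The concern.** An intervention subscriber must have signed up at least six weeks before the survey that counts. A control signs up inside the window and is surveyed at once. The two groups are therefore drawn from sign-up periods that are offset in time, and nothing in the design balances them.

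Recruitment passes through a ministry, a Lusaka association, district boards and individual school heads. Such channels could plausibly bring in teachers in clusters, so the mix of city, school level and workload could differ between the two periods. The protocol itself expects characteristics of this kind to go with the outcomes. It plans adjustment where it describes associations, but states none where it estimates an effect.

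This is the only estimate with a comparison group, and the Conclusions look to the study for evidence of effectiveness to inform policy. The Limitations section does not mention that the cohorts may not be comparable. A shift in mix could create a benefit or hide one.

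**Working it through.** The plan gives no sample size, effect estimate or power for this contrast, so there is no figure to reproduce. The check asks how far the groups overlap, and what a shift in mix would then produce if the programme had no effect.

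**Overlap.** Take a 13-week window with even sign-up (assumed).

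- Controls sign up in weeks 0 to 13.
- In the example window, which opens at the anticipated January 2023 launch, 6-week surveys fall in weeks 6 to 13 and come from sign-ups in weeks 0 to 7. Every intervention subscriber is then also a new subscriber in the window.
- In a window well after launch, 6-week surveys fall in weeks 0 to 13 and come from sign-ups in weeks -6 to 7.
- In both cases the shared sign-up weeks are 0 to 7, which is 7/13 = 54% of the control period. The non-shared part is 6/13 = 46%.

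**Spurious difference with no true effect.** The shared part contributes the same mix to both groups, so

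spurious difference = (6/13) x (shift in mix between the non-shared periods) x (prevalence gap between the strata).

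The shift and the gap are assumptions; the documents give neither. The reference prevalence is the 35.3% for depressive symptoms cited in the Background. The hypothesised 20% reduction of it is 0.20 x 35.3 = 7.06 points.

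| Shift (points) | Gap (points) | Shift x gap | x 6/13 | Relative to 35.3% |
|---|---|---|---|---|
| 10 | 10 | 1.0 | 0.5 | 1% |
| 20 | 20 | 4.0 | 1.8 | 5% |
| 30 | 15 | 4.5 | 2.1 | 6% |
| 40 | 20 | 8.0 | 3.7 | 10% |

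The last two rows amount to 2.08/7.06 = 29% and 3.69/7.06 = 52% of the hypothesised effect. To imitate all of it, shift x gap would have to reach 7.06 x 13/6 = 15.3 points, for example a 51-point shift with a 30-point gap.

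**False-positive rate.** Assume 40% control prevalence, 993/4 = 248 controls, and between 248 x 7/13 = 134 and 248 intervention responders. A two-sided pooled test of two proportions at 5%, treating all records as independent, rejects in about 7% of trials for a spurious 2-point difference and in 12% to 15% for 4 points.

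**Calendar time.** In the launch window the mean survey week is (0+13)/2 = 6.5 for controls and (6+13)/2 = 9.5 for the intervention group, an offset of 3 weeks. In a later window both groups are surveyed across weeks 0 to 13 and the offset disappears.

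**The case against.** The strongest reply has four parts.

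- **The text is silent on adjustment; it does not rule it out.** The protocol names neither a test nor a model for this contrast, and an analysis plan that is not shown could add covariates. This stands as a caution about wording: a reader might infer that the protocol commits to an unadjusted analysis, and it does not say so. It does not dispose of the point. The same section specifies adjustment for the correlate models and states only a comparison of prevalence and means here. Followed as written, the contrast has no protection.
- **The groups are not separate waves.** This stands. A reader might treat them as disjoint early and late cohorts and take shift x gap in full: 4.5 to 8 points, or 13% to 23% of 35.3%, enough to match the whole hypothesised effect. The overlap does not support that; the same assumptions give 2.1 to 3.7 points.
- **No sequence of recruitment by city, and no city-specific prevalence, is documented.** This also stands. The Hypothesis section names teacher and organisational factors and class size, not city. The mechanism is plausible, but its size is assumed.
- **The contrast is not the primary analysis.** Correct. Outcomes and Measures defines the primary outcomes as changes from baseline among subscribers, and fixed city and school traits cancel in a paired comparison. A reader should not infer that the primary outcomes are confounded in this way. Those analyses have no control group, however, so this contrast still carries weight of its own.

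**Conclusion.** The point holds in a limited form. In a non-randomised design, the one between-group estimate compares staggered, partly overlapping sign-up cohorts. No adjustment is stated for it, although the protocol expects the outcomes to vary with characteristics on which those cohorts could differ.

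Under even sign-up, a 30-40 point shift and a 15-20 point gap, the spurious difference is about 2 to 4 points, or 6% to 10% of a 35.3% prevalence. That is enough to distort a hypothesised 7-point effect, but not to account for it. With a 10-point shift and a 10-point gap it is at most 1 point, even if the overlap is ignored. The direction cannot be foreseen.

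The overlap also raises a second matter. In the example window, one teacher can supply both a control baseline and a 6-week score. An analysis that treats these records as independent would give wrong standard errors.

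The 3-week calendar offset belongs to the launch window only, and the documents do not show that scores move over three weeks.

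**What to change.** In Statistical Analysis, replace the plain comparison with a prespecified regression of outcome on group, linear for scores and logistic for prevalence. Then:

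- **Adjust** for the collected demographic and work-related variables, named in advance: for example city, school level, age, sex, and class size or workload where collected, together with calendar time of survey. Data Collection does not itemise these. City is implied by eligibility, and school level by the separate correlate analyses for elementary and high school teachers; the others should be checked against the questionnaire.
- **Handle teachers who qualify for both groups.** Either assign each teacher to one group by a stated rule, or keep both records and account for the repetition, for example with GEE or cluster-robust standard errors by teacher.
- **Show the intervention cohort's own enrolment scores** beside the controls' enrolment scores, so that readers can see whether the cohorts were alike before exposure.
- **Describe the contrast as supplementary**, and say that residual confounding remains possible. Adjustment deals only with what is measured.

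The cost is a few degrees of freedom and slightly more analysis work. No new data are needed for variables already in the questionnaire, and survey dates should be available from the web platform.
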